## 3. Research Objectives and Hypotheses

### 3.1 Primary Objectives

1. To determine the optimal MRD threshold for predicting 5-year event-free survival following Induction Course 1 and Course 2 chemotherapy using ROC curve analysis.
2. To compare the prognostic discrimination capacity of the traditional 0.1% MRD threshold versus a proposed 0.05% threshold through Kaplan-Meier survival analysis and hazard ratio calculations.
3. To quantify the improvement in risk classification accuracy using net reclassification improvement (NRI) analysis when applying the lower MRD threshold.

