### 4.2 Data Source

The Therapeutically Applicable Research to Generate Effective Treatments (TARGET) initiative database, version dated April 28, 2021, containing comprehensive clinical and laboratory data from pediatric AML patients treated between September 1996 and December 2016.

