### 4.3 Study Period

Data collection period: September 1996 to December 2016 Analysis period: January 2025 to June 2025

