## 5. Study Population

### 5.1 Inclusion Criteria

- Pediatric patients (<18 years at diagnosis) with newly diagnosed de novo AML (non-M3 subtype)
- Availability of MFC-MRD data measured after completion of Induction Course 1 and/or Course 2
- Treatment according to one of the specified protocols: AAML03P1, AAML0531, or AAML1031
- Complete baseline clinical and molecular characterization data
- Minimum follow-up duration of 36 months for surviving patients

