## 7. Statistical Analysis Plan

### 7.1 Primary Analysis

**Survival Analysis**: Kaplan-Meier method will be used to estimate EFS distributions stratified by MRD status at both thresholds. The log-rank test will compare survival curves.

**ROC Analysis**: Receiver operating characteristic curves will determine the optimal MRD threshold for predicting 5-year EFS status using Youden's index.

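### The ROC curve for the MRD cut-off needs a known EFS status at 60 months, but the follow-up rule and data version leave that status unknown for some event-free patients, and the protocol does not say how they are classed

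*Protocol*

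**What the plan says.** The first primary objective (protocol 3.1) is "To determine the optimal MRD threshold for predicting 5-year event-free survival following Induction Course 1 and Course 2 chemotherapy using ROC curve analysis". Section 7.1 carries it out: "Receiver operating characteristic curves will determine the optimal MRD threshold for predicting 5-year EFS status", with the cut-off chosen by Youden's index. EFS runs from diagnosis to the first event (6.3).

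On follow-up, 5.1 requires "Minimum follow-up duration of 36 months for surviving patients". Section 5.2 excludes patients whose follow-up is insufficient but gives no number of months. Section 4.2 describes the source as a "version dated April 28, 2021" that holds "pediatric AML patients treated between September 1996 and December 2016".

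No section says how a patient who is event-free at last contact before 60 months enters the ROC analysis. The sensitivity analyses in 7.3 (imputation, a landmark and competing risks) are not tied to 5-year status.

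**The concern.** An ordinary ROC curve on a status at a fixed time needs every patient labelled as a case or a control at that time. Here the horizon is 60 months and the follow-up guaranteed for survivors is 36. Kaplan-Meier, log-rank and Cox analyses handle the resulting censoring; an ordinary ROC does not. The analyst must either drop the unlabelled patients, a selection that depends on outcome, or label them event-free, which is wrong for some.

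The stake is the first primary objective. The study must separate two neighbouring cut-offs of one marker, 0.05% and 0.1%, so even a small selection effect matters if it acts differently on patients above and below them. The cohort pools three treatment protocols, and the latest patients are the ones who lose event-free status.

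**Working it through.** The protocol gives no figure for this point. Its only power statement (5.3, hazard ratio 2.0) concerns a different analysis.

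**1. Longest possible follow-up.** Inputs: data version 28 April 2021, last entries December 2016 (4.2). From 1 December 2016 this is 52.9 months, and from 31 December 2016 it is 51.9 months. Nobody diagnosed after 28 April 2016 can be observed event-free at 60 months. That is a window of 8.1 months.

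**2. Share with unknown status.** Accrual by year and loss to follow-up are not given, so both are assumed. Let *S* be 5-year EFS, *w* the share diagnosed in the last 8.1 months and *λ* the annual loss rate. Treating later failures as negligible,

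unknown share ≈ *S*[*w*·e^(−3λ) + (1−*w*)(e^(−3λ) − e^(−5λ))] / [1 − *S*(1 − e^(−3λ))].

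Take *S* = 0.571 (42.9% events), inside the 50-60% EFS quoted in section 2.

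| Accrual | *w* | *λ* = 1% | *λ* = 5% |
|---|---|---|---|
| Even over all 244 months | 8.1/244 = 0.033 | (0.0184 + 0.0106)/0.983 = 3.0% | (0.0163 + 0.0452)/0.921 = 6.7% |
| Last 68.4 months only (follow-up 4.3 to 10 years) | 8.1/68.4 = 0.118 | (0.0656 + 0.0097)/0.983 = 7.7% | (0.0582 + 0.0412)/0.921 = 10.8% |

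Simulations that include later failures gave 3.1-7.5% and 8.1-11.4%. Of 1,205 patients, the formula gives about 36 to 130.

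**3. What dropping or coding does to the labels.** Among patients diagnosed after 28 April 2016, dropping the unknowns removes every non-event. In the whole cohort it removes almost only non-events: in simulation with the 4.3-10-year window, 0.4-3.3% of the unknowns failed before 60 months, about 0.4 to 5 of 1,205. Those few are the ones mislabelled if all unknowns are coded event-free.

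**4. Effect on the event fraction.** If a share *c* of 5-year survivors has no status, complete-case EFS is *S*(1−*c*)/[*S*(1−*c*) + 1 − *S*]. With *S* = 0.55 and *c* = 0.067, 0.134 and 0.20, it is 53.3%, 51.4% and 49.4%.

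**5. Effect on the cut-off when censoring is unrelated to MRD.** Sensitivity and specificity are conditional on outcome, so the event fraction does not enter Youden's index. In a simulation of 1,205 patients with an assumed MRD distribution, the median Youden cut-off moved by less than 0.004 percentage points and the AUC by less than 0.003, under either dropping or coding as event-free. Sampling error was far larger: with every status known, the middle 90% of cut-offs ran from about 0.014% to 0.13%.

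**6. Effect when MRD differs by era.** Let *q* be the MRD-positive share among event-free patients. Dropping the late ones changes specificity by *w*(*q*_late − *q*_early). For an assumed difference of 10 points, this is 0.033 × 10 = 0.3 points or 0.118 × 10 = 1.2 points.

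If loss also depends on MRD, the shift can be larger. Suppose true specificity is 80%, and status is missing for 10% of MRD-negative and 30% of MRD-positive survivors (assumed). Complete-case specificity is then 0.72/(0.72 + 0.14) = 83.7%, an error of 3.7 points.

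**7. NRI.** For two cut-offs of one marker on a binary status, the categorical NRI is the change in sensitivity plus the change in specificity. It is therefore equally insensitive to the event fraction and equally open to step 6, if it uses the same 5-year status.

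**The case against.** The strongest reply is that the cut-off is not shown to move. Section 7.1 uses the ROC only to choose a threshold, and step 5 finds almost no change when censoring is unrelated to MRD. That stands, and it limits the severity.

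The shift in the event fraction also falls on quantities the protocol does not plan: it lists no predictive values or crude 5-year proportions, and EFS is estimated by methods that allow for censoring. That stands too.

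A third reply is that the wording does not exclude a time-dependent ROC, which a separate analysis plan might name. This stands only in part. Section 7 is itself headed as the statistical analysis plan, and it sets a status at 5 years beside a 36-month follow-up rule. The text needs aligning even if the intended method is sound.

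A reader might infer that the latest patients can count only as cases. That is true only for diagnoses after 28 April 2016, and only if unknowns are dropped, which the protocol does not say. Section 4.2 gives dates of treatment rather than diagnosis; if the last diagnosis came before that date, this part falls away and the gap between 36 and 60 months remains. A reader might also infer that the NRI is necessarily affected, but 7.2 gives it no horizon.

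Finally, 4.3 states "Data collection period: September 1996 to December 2016". Read as the end of follow-up, this would leave everyone diagnosed after December 2011 without an observable event-free status, about 60/244 × 1,205 = 296 patients under even accrual. The documents do not support that reading over the 2021 version date, but the two sections should be reconciled.

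**Conclusion.** The mismatch is real and internal to the protocol: a 60-month status, a 36-month minimum, and a data version that reaches at most about 52 to 53 months for the last entries. As written, the first primary objective requires a choice about censored patients that the protocol does not state.

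The share affected is about 3-7% under even accrual and 8-11% under late accrual, both resting on assumed annual loss of 1-5%. A materially wrong cut-off is not shown. The cut-off hardly changes if censoring is unrelated to MRD; a bias of roughly a point or more in specificity needs MRD or censoring to vary by era or treatment protocol, which the documents neither establish nor rule out. The Kaplan-Meier, log-rank and Cox analyses are not affected. This is a change that should be made, not one that invalidates the plan.

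**What to change.** In 7.1, specify a cumulative/dynamic time-dependent ROC at 60 months, estimated with inverse-probability-of-censoring weights that may depend on treatment protocol, or with a Kaplan-Meier-based estimator. Take Youden's index from that curve. State in one sentence that patients censored before 60 months are neither dropped nor coded event-free. In 7.2, state the NRI's horizon; if it is 5 years, use the censored-data form. In 4.3, say whether the period ending December 2016 refers to enrolment or to follow-up.

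The cost is slightly wider confidence intervals and a little more analysis work. No new data are needed, and the R software already named in 7.4 can be used.

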### 7.2 Secondary Analyses

**Cox Regression**: Univariate and multivariate Cox proportional hazards models will assess the association between MRD thresholds and EFS, adjusting for relevant covariates. **Net Reclassification Improvement**: Categorical NRI will quantify improvement in risk prediction using the novel threshold. **Subgroup Analysis**: Consistency of the MRD threshold will be evaluated within predefined genetic risk categories.

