## 2. Research Background and Scientific Rationale

Pediatric acute myeloid leukemia represents a heterogeneous group of hematologic malignancies characterized by clonal proliferation of myeloid precursors with impaired differentiation. Despite significant advancements in risk-adapted therapy approaches, including allogeneic hematopoietic stem cell transplantation for high-risk patients, relapse remains the predominant cause of treatment failure, with 5-year event-free survival rates plateauing at approximately 50-60% in contemporary clinical trials. Minimal residual disease monitoring has emerged as a critical component of modern risk stratification in acute leukemias. Among various MRD detection methodologies, multiparametric flow cytometry-based MRD assessment offers the advantage of rapid turnaround time, widespread availability, and applicability to nearly all patients regardless of genetic markers. The conventionally accepted threshold of 0.1% for defining MRD positivity has demonstrated prognostic utility across multiple studies, yet evolving technological capabilities in flow cytometry warrant reevaluation of this standard. Recent evidence suggests that lower levels of residual disease, previously classified as MRD-negative by the 0.1% threshold, may still harbor significant prognostic implications. Technological advancements now enable reliable detection of leukemic cells at levels as low as 0.01%, raising important questions about the optimal threshold for clinical decision-making. This study addresses a critical evidence gap by systematically evaluating a lower MRD threshold in a large, well-annotated pediatric AML cohort.

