### 3.2 Secondary Objectives

1. To validate the consistency of the proposed 0.05% MRD threshold across established genetic risk subgroups (low-risk, standard-risk, high-risk).
2. To establish the independent prognostic value of the novel MRD threshold through multivariate Cox regression analysis adjusting for known clinical and molecular variables.
3. To assess the clinical utility of the lower threshold in guiding treatment decisions, particularly regarding transplantation candidacy.

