### 3.3 Research Hypotheses

- **Primary Hypothesis**: An MRD threshold of 0.05% provides superior prognostic discrimination compared to the conventional 0.1% threshold for predicting 5-year EFS in pediatric AML.
- **Secondary Hypothesis**: The 0.05% threshold demonstrates consistent prognostic performance across all genetic risk categories and offers significant net reclassification improvement.

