### 6.3 Variable Definitions

- **Event-free survival (EFS)**: Time from diagnosis to first event (induction failure, relapse, secondary malignancy, or death from any cause)
- **MRD positivity**: Defined using two thresholds: traditional (≥0.1%) and novel (≥0.05%)
- **Complete remission**: <5% blasts in morphologically normal bone marrow with recovery of peripheral counts
- **Genetic risk groups**:
  - Low risk: inv(16)/t(16;16) or t(8;21)
  - High risk: monosomy 7 or del(5q)
  - Standard risk: All other cases with adequate cytogenetic data

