### 8.4 Risk-Benefit Assessment

**Risks**: Minimal risk study; potential breach of confidentiality mitigated by de-identification and secure data handling. **Benefits**: No direct benefits to participants; potential improvement in risk stratification for future pediatric AML patients.

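### Lowering the cut-off can only move patients up, so the single summed NRI restates the change in Youden's index and masks lost specificity; report its two parts

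*Protocol*

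**What the plan says.** All references are to the protocol.

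- Section 7.2 plans one reclassification index: "Categorical NRI will quantify improvement in risk prediction using the novel threshold". It does not define the risk categories.
- Section 3.1, objective 3, gives the index primary rank: "To quantify the improvement in risk classification accuracy using net reclassification improvement (NRI) analysis when applying the lower MRD threshold". Section 7.2 lists the same analysis as secondary.
- Section 3.3 includes in its secondary hypothesis that the lower threshold "offers significant net reclassification improvement".
- Section 6.3 defines MRD positivity at 0.1% or above and at 0.05% or above. The definitions are nested: everyone positive under the first is positive under the second.
- Section 7.1 uses ROC curves to find the "optimal MRD threshold for predicting 5-year EFS status using Youden's index".
- Section 2 gives "5-year event-free survival rates plateauing at approximately 50-60% in contemporary clinical trials". This is background; the cohort's own event rate is not stated.

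**The concern.** A reader who sees a positive net reclassification improvement will take it that the new classification sorts patients better overall. With two nested cut-offs, the index is a trade-off with a fixed direction. Lowering the cut-off can gain sensitivity and can lose specificity; neither can go the other way. Adding the two without weights gives one figure in which the cost is no longer visible, and sections 3.1 and 7.2 call that figure improvement.

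Two things are at stake. First, the NRI may be presented as a further line of evidence for 0.05% beside the ROC result, when it is the same quantity. Second, the sum can be positive although more event-free patients than event patients were newly called positive, and a reader of the sum alone could not tell.

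**Working it through.** **Inputs.** The cut-offs are those of section 6.3. The cohort size is 1,205 (sections 1 and 5.3). EFS of 50-60% comes from section 2, so the assumed 5-year event rate is 40-50%. The outcome is 5-year EFS status, stated for the ROC analysis in section 7.1 and assumed here for the NRI. The number of patients between 0.05% and below 0.1% is not given, so every count in that band below is assumed. The protocol states no NRI figure to reproduce.

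**Step 1: direction of movement.** The two-category NRI is

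NRI = [P(up | event) − P(down | event)] + [P(down | no event) − P(up | no event)].

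With nested cut-offs both down terms are zero. Let E patients have an event and N not, and let e and n of them lie in the band. Then

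NRI = e/E − n/N.

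The event part e/E is at least 0 and the non-event part −n/N is at most 0.

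**Step 2: identity with Youden's index.** J = sensitivity + specificity − 1. Lowering the cut-off raises sensitivity by e/E and lowers specificity by n/N, so the change in J is e/E − n/N, which is the NRI. If the ROC analysis selects 0.05% as the maximum of J, the NRI against 0.1% in the same patients, at the same time point and with the same outcome, cannot be negative.

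**Step 3: when the sum is positive.** e/E > n/N is equivalent to e/(e+n) > E/(E+N): the event share in the band must exceed the cohort event rate. Equivalently, n/e must stay below N/E.

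| EFS | E / N (of 1,205) | Largest n per e before the sum reaches 0 | Event share giving a positive sum with a non-event majority |
|---|---|---|---|
| 60% | 482 / 723 | 723/482 = 1.50 | 40-50% |
| 55% | 542 / 663 | 663/542 = 1.22 | 45-50% |
| 50% | 602 / 603 | 603/602 = 1.00 | none |

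The window widens where EFS is higher: 30-50% at an assumed EFS of 70%, and 20-50% at 80%. This matters if the NRI is also computed within genetic risk groups.

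**Step 4: examples (assumed counts).**

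- 1,000 patients, 450 events, 60 in the band (28 events, 32 without): 28/450 − 32/550 = 0.0622 − 0.0582 = +0.004. The band's event share is 28/60 = 46.7%, against 45% in the cohort.
- 1,205 patients, EFS 60%, 100 in the band (45 and 55): 45/482 − 55/723 = 0.0934 − 0.0761 = +0.017, although 55% of those moved are event-free at 5 years. At 40 and 60 the sum is exactly 0.
- The same 45 and 55 at EFS 55%: 45/542 − 55/663 = about 0.000. With 48 and 52 it is +0.010.
- The same 45 and 55 at EFS 50%: 45/602 − 55/603 = −0.016.

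**Step 5: could such a sum be significant?** A simple standard error is √(e/E² + n/N²).

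- 28 and 32: √(28/450² + 32/550²) = 0.016, z = 0.26, 95% CI about −0.027 to +0.035.
- 45 and 55 at EFS 60%: √(45/482² + 55/723²) = 0.0173, z = 0.0173/0.0173 = 1.0. Reaching z = 1.96 at this share takes about 100 × 1.96² = 384 patients in the band.
- 49 and 51 at EFS 60%: NRI = 0.1017 − 0.0705 = 0.031, SE 0.0176, z = 1.77. Reaching 1.96 takes about 100 × (1.96/1.77)² = 123 patients.

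A positive sum with a non-event majority is thus easy to obtain. A significant one needs a large band and an event share close to 50%.

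**The case against.** The strongest reply has five parts.

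1. **The index is informative.** A positive sum means the newly positive have above-average risk for the cohort. This stands. Requiring an event majority among them would be a value judgement, and the point does not rest on it.
2. **The NRI is not alone.** It sits beside ROC, Kaplan-Meier, hazard-ratio and Cox analyses. A reader might infer that the cost of the lower cut-off appears in no result. The protocol does not support that: Youden's index counts false positives, and the Kaplan-Meier curves at both thresholds show outcome among positives under each definition. What remains is that the NRI sum itself does not show the cost.
3. **The significance test protects the claim.** Section 3.3 expects a significant NRI, and the examples with a non-event majority in step 5 fall short of it. This stands and limits the size of the point. It does not affect the identity with Youden's index.
4. **The categories are undefined.** With categories of model-predicted risk, patients could also move down. This is true, so the point is conditional. MRD positive and negative is nevertheless the natural reading of objective 3 with section 6.3.
5. **Component reporting belongs in a statistical analysis plan that is not shown.** Its absence alone is no finding. The choice of index and the label of improvement are, however, already fixed in sections 3.1, 3.3 and 7.2.

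A reader might also link the NRI to section 3.2, which aims "To assess the clinical utility of the lower threshold in guiding treatment decisions, particularly regarding transplantation candidacy". No section makes that link, and no analysis is named for that aim.

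**Conclusion.** The point holds as a cheap improvement to how the chosen index is presented, not as an error in the plan. Given MRD positive and negative as the categories, and the same patients, time point and outcome handling as in the ROC analysis, it is exact that movement is upward only, that the non-event part is never above zero, and that the sum equals the change in Youden's index. Calling that sum improvement counts the ROC result a second time and hides the loss of specificity inside a net figure.

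The risk of a misleading sign is real but narrow. On the background EFS it needs a 5-year event share of 40-50% in the band at 60% EFS or 45-50% at 55%, and it cannot occur at 50%. The cohort's own rate and the size of the band are unknown.

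A reader might want section 8.4 rewritten because it mentions "potential improvement in risk stratification for future pediatric AML patients". That is a cautious risk-benefit statement for an analysis of de-identified data. It makes no claim about reclassification and needs no change.

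**What to change.** In section 7.2:

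- state that the NRI categories are MRD positive and negative at each cut-off;
- report the event NRI and the non-event NRI separately, each with the counts moved and a confidence interval;
- give the 5-year event proportion among patients from 0.05% to below 0.1%;
- state that the summed NRI alone will not be taken as evidence of improvement or of clinical utility.

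Align objective 3 in section 3.1 and the secondary hypothesis in section 3.3 with this, so that both refer to the two components rather than to the sum.

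The cost is wording only, because both parts must be computed to obtain the sum. The downside is a less favourable-looking headline, since the non-event part can only be zero or negative.

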### 5.3 Sample Size Justification

The initial TARGET-AML cohort included 1,205 pediatric patients with non-M3 AML. Based on power calculations for detecting a hazard ratio of 2.0 for EFS with 80% power at α=0.05, the available sample size provides adequate statistical power for the proposed analyses. The cohort characteristics demonstrate balanced representation across key prognostic subgroups.

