## 6. Methods

### 6.1 Data Collection Procedures

Data will be extracted from the TARGET database using standardized data collection forms. The following variable categories will be included:

- **Demographic data**: Age at diagnosis, gender, ethnicity
- **Disease characteristics**: WBC count at diagnosis, bone marrow and peripheral blast percentages, FAB classification, central nervous system involvement status
- **Genetic markers**: Karyotype, FLT3-ITD, NPM1, CEBPA, and WT1 mutation status
- **Treatment data**: Chemotherapy protocol, response assessment after each induction course, stem cell transplantation details
- **MRD data**: Quantitative MRD levels after Induction Courses 1 and 2
- **Outcome data**: Event-free survival, overall survival, relapse details

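### Consistency of the 0.05% threshold across genetic risk groups is to be judged within each group; the plan names no between-group comparison, and the power statement is not shown to cover this hypothesis

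*Protocol*

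**What the plan says.** The aim is stated twice. Secondary objective 1 (Protocol 3.2) is "To validate the consistency of the proposed 0.05% MRD threshold across established genetic risk subgroups", naming low, standard and high risk. The secondary hypothesis (3.3) goes further: "The 0.05% threshold demonstrates consistent prognostic performance across all genetic risk categories".

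The matching analysis is one sentence in section 7.2: "Consistency of the MRD threshold will be evaluated within predefined genetic risk categories". It mentions no MRD-by-risk-group interaction, no estimate of heterogeneity and no criterion for what counts as consistent.

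Section 6.3 forms the three groups from cytogenetics. Low risk is defined by the core-binding-factor changes and high risk by two findings, monosomy 7 or del(5q). The remainder is "Standard risk: All other cases with adequate cytogenetic data".

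Section 5.3 gives a single power basis, "detecting a hazard ratio of 2.0 for EFS with 80% power at α=0.05". It concludes that the sample is adequate for the proposed analyses in general and that the key prognostic subgroups are represented in a balanced way. No patient or event counts by risk group appear anywhere in the protocol.

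**The concern.** Consistency is a statement about differences between groups. Three separate hazard ratios or log-rank tests, each read on its own, do not address it. Precision in each group depends on its number of events, so a large group will usually show a clear effect and a small group often will not, even when the underlying hazard ratio is identical.

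Two wrong conclusions are possible. A threshold that works equally well everywhere may be reported as failing in high-risk disease because that group is small. Conversely, similar-looking point estimates with wide intervals may be reported as proof of consistency. The section 5.3 statement may also lead a reader to think the subgroup hypothesis has been covered by a power calculation, when the protocol shows none for it.

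**Working it through.** **Inputs from the protocol.** N = 1,205; hazard ratio 2.0, 80% power, α = 0.05 (5.3; two-sided assumed, as sidedness is not stated); 5-year EFS of about 50-60% (section 2), hence 40-50% with an event.

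**Inputs assumed, because the protocol gives none.** High-risk share 3-8% (10% as an upper variant); event rate in high risk 50-70%; MRD-positive share 25-50%; standard-risk share 65-72% with 50% events.

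**Step 1: the protocol's own figure, whole cohort.** Schoenfeld's formula for the events d needed, with MRD-positive share p:

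d = (1.960 + 0.842)² / [p(1 − p)(ln 2)²]

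- p = 0.50: 7.85 / (0.25 × 0.480), which rounds up to 66 events
- p = 0.25: 88 events
- p = 0.10: 182 events

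The cohort would supply 1,205 × 0.40 to 0.50 = 482 to 602 events. Power exceeds 99% in every variant. The adequacy statement is therefore right for the whole-cohort main effect, although the protocol states no required number of events to compare with.

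**Step 2: power inside each group if the hazard ratio is 2.0 everywhere.**

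Power = Φ( √[d·p(1 − p)] × ln 2 − 1.96 )

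| High-risk share (assumed) | Patients | Events (50-70%) | Power (p = 0.25-0.50) |
|---|---|---|---|
| 3% | 36 | 18-25 | 25-41% |
| 5% | 60 | 30-42 | 38-61% |
| 8% | 96 | 48-67 | 55-81% |

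Lowest corner: √(18.1 × 0.1875) × 0.693 − 1.96 = −0.68, so power is 25%. Highest corner: √(67.5 × 0.25) × 0.693 − 1.96 = 0.89, so power is 81%.

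Standard risk at 65% of 1,205 has 783 patients and, at 50% events, 392 events. With p = 0.25, √(392 × 0.1875) × 0.693 − 1.96 = 3.98, so power is above 99%.

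For 80% power the high-risk group would need 66 / 0.70 = 95 to 88 / 0.50 = 176 patients, that is 8-15% of 1,205. All counts are before exclusions; the schema in 4.5 applies eligibility after the figure of 1,205.

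**Step 3: width of the high-risk estimate.** SE(log HR) = 1 / √[d·p(1 − p)].

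- 36 patients, 60% events (21.7), p = 0.25: SE = 0.496, factor exp(1.96 × 0.496) = 2.64. Around a hazard ratio of 2.0 the 95% interval is 0.76 to 5.3.
- 96 patients, 60% events (57.8), p = 0.40: SE = 0.268, factor 1.69, interval 1.2 to 3.4.

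**Step 4: would an interaction test solve it?** High risk (60% events, p1 = 0.25-0.40) against the rest (45% events, p0 = 0.25):

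SE = √{ 1/[d1·p1(1 − p1)] + 1/[d0·p0(1 − p0)] }

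| High-risk share | Power for a two-fold ratio of hazard ratios | Ratio detectable with 80% power |
|---|---|---|
| 3% | 28-34% | 3.5-4.1 |
| 5% | 42-50% | 2.7-3.0 |
| 8% | 58-67% | 2.2-2.5 |
| 10% | 66-75% | 2.1-2.3 |

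The interaction model asks the right question, but a non-significant result from it would not establish consistency.

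**The case against.** Section 7.2 is short. It does not say that consistency will be judged by significance in each group, and it does not rule out an interaction term, which a separate analysis plan could supply. This is fair, and it limits the point to what is written. But section 7 itself carries the title of the statistical analysis plan, and the one method it names for this hypothesis stays within groups.

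A reader might infer something stronger: that only a handful of high-risk patients are informative, so the hypothesis cannot be supported at all. The protocol does not bear this out. It gives neither the high-risk share nor the share with MRD from 0.05% to below 0.1%. If both were 3-8%, 1-8 high-risk patients would change class (36 × 0.03 to 96 × 0.08). That count, however, concerns 0.05% against 0.1%, which is the primary hypothesis. The consistency hypothesis asks whether the 0.05% cut is prognostic in each group, and there every high-risk patient with MRD data contributes: 36-96 on the same assumptions.

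A reader might also fault the risk groups because FLT3-ITD, NPM1, CEBPA and WT1 are collected (6.1) but do not define them. That is a declared choice rather than an error. The idea that standard risk mixes opposite prognoses would rest on titles in the reference list alone, and adjustment for molecular variables is already foreseen in secondary objective 2.

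**Conclusion.** The point holds as a mismatch between hypothesis and analysis. The protocol claims consistency across all risk groups and plans only evaluation within them. This part needs no assumption.

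The size of the problem is conditional. With a common hazard ratio of 2.0 and an assumed high-risk share of 3-8%, power in that group is about 25-81%, against over 99% in a large standard-risk group. At the lower shares, a truly uniform effect would more often than not miss significance in high risk. If the high-risk group were 15% of the cohort or more, this imbalance would largely disappear, but the need for a between-group comparison would remain.

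Section 5.3 is correct for the whole-cohort comparison and unsupported for this hypothesis. The balance it asserts cannot be checked without counts. As this is a secondary hypothesis and the remedy is cheap, the change should be made but does not endanger the primary analysis.

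**What to change.** - **Section 7.2:** fit one Cox model for EFS with MRD at 0.05%, risk group and their interaction. Report the ratios of hazard ratios with 95% confidence intervals, the group-specific hazard ratios with intervals, and patients and events per group. State that consistency will not be inferred from significance within groups or from a non-significant interaction.
- **Section 3.3 (and the matching objective in 3.2):** reword to estimating how far the prognostic effect of the 0.05% threshold differs between risk groups. Treat the high-risk result as exploratory if its interval is wide. If the word consistent is kept, state beforehand what range of the ratio would qualify.
- **Section 5.3:** limit the power statement to the whole-cohort comparison, and support the claim of balanced subgroups with counts or remove it.

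The cost is a few sentences and one model on variables already collected. The downside is a more modest secondary claim: with about 28-75% power for a two-fold ratio of hazard ratios at assumed high-risk shares of 3-10%, the interaction analysis will describe heterogeneity rather than settle it.
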